### Statistical Analysis

Data will be maintained centrally at Flinders University with double entry of data into SPSS software to verify accuracy. Primary analysis for this study will be undertaken using intention to treat principles. Location of central tendency and distribution will be determined and data presented as appropriate. Independent sample t-tests, Mann-Whitney U tests and Chi-square test of association will be used as appropriate to compare groups at baseline. To determine differences between the groups at the primary end-point (six months), and at 12 month follow up ANCOVA or logistic regression will be used with models adjusted according to potential confounders. The analyses will be undertaken by a statistician blinded to group allocation.

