### Measurements and Procedures

#### Baseline, six and 12 month follow-up

Project personnel will assess the selected outcome measures at baseline (prior to randomisation) whilst an individual masked to treatment allocation will assess outcomes at six and 12 months. Testing will coincide with maximum effect of each participant's analgesic regime. Outcome measures have been selected based on suitability for older adults following PFF, strength of the evidence to support validity and reliability, significance to rehabilitation and previous use in the literature.

The baseline assessment protocol entails a detailed multi-dimensional health assessment by means of:

**a) Physical Function, Strength and Balance: **Physical autonomy will be measured using a physical and instrumental ADL scale [31]. A subjective rating of pain for three separate activities of daily living (ADL) will be established prior to physical testing, which include knee extensor strength using a Nicholas Manual Muscle Tester (NMMT) [32] and a 30 second chair stand test [33], gait speed via a 3 m Walk Test [34], balance on the modified Berg Balance Scale (MoBerg) [35] and grip strength using a hand held dynamometer [36].

**b) Body Composition and Nutrition Measures: **Percent weight change will be assessed using calibrated scales. Body composition (fat free mass) will be measured at baseline, six and 12 months using dual-energy x-ray absorptiometry (DEXA: Lunar Prodigy, GE Healthcare, UK). Lumbar spine and proximal femur DEXA scans will also be performed to assess changes in bone mineral density. Triceps skinfold measures and mid upper arm circumference (MUAC) will also be measured to determine corrected arm muscle area (CAMA) [37]. Appetite will be assessed using the Council on Nutrition Appetite Questionnaire (CNAQ) [38] and 24 hour dietary recall recorded using a standardised protocol [39].

**c) Questionnaires: **Assessment of Quality of Life Instrument (AQoL) [40], a four item summary scale created from the CES-D [41] to determine positive affect and a self rated health survey. In addition caregivers will also complete a caregiver burden and strain index [42,43].

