#### Additional Information

Monitoring of participants for six months via weekly home visits will allow for an account of any change in accommodation, falls and injuries and any change in health status. At 12 months participants will be contacted via telephone to organise the follow-up assessment. If there is no response then project personnel will contact the next of kin.

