### Sample Size Considerations

Gait speed at six months was chosen as the primary outcome because safe, independent walking is a high priority amongst patients participating in rehabilitation, and gait speed is often recommended as a measure of status and outcome [46,47]. Using gait speed data collected from a recent study undertaken at the Adelaide site (n = 100) [28] it was calculated that a sample size of 176 participants per group will achieve a statistically and clinically significant 20% difference between the two groups (power 80%, alpha = 0.05). To allow for deaths and withdrawals (30%), 460 participants will be recruited, 230 per group.

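### The stand-alone 12-month ANCOVA, as named, makes no use of six-month values from people not reassessed at 12 months; a repeated-measures model or suitable imputation would give a modest gain

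*Protocol article*

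**What the plan says.** All references are to the Protocol article.

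- **Assessment times.** After baseline, "an individual masked to treatment allocation will assess outcomes at six and 12 months" (Baseline, six and 12 month follow-up). Each outcome therefore has two post-baseline values.
- **Primary outcome.** "Gait speed at six months was chosen as the primary outcome" (Sample Size Considerations). The 12-month comparison is secondary.
- **Analysis.** For differences at six months "and at 12 month follow up ANCOVA or logistic regression will be used", with adjustment for potential confounders (Statistical Analysis). No repeated-measures model is named.
- **Principle.** "Primary analysis for this study will be undertaken using intention to treat principles" (Statistical Analysis). The article neither states nor rules out a complete-case analysis or imputation.
- **Contact.** Home visits are weekly for six months. After that, "At 12 months participants will be contacted via telephone to organise the follow-up assessment" (Additional Information), with the next of kin approached if there is no response.
- **Loss.** "To allow for deaths and withdrawals (30%), 460 participants will be recruited, 230 per group" (Sample Size Considerations). The allowance covers deaths and withdrawals together.

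**The concern.** The 12-month comparison shows whether any benefit outlasts the programme. The Discussion itself cites evidence that training gains fade once a programme stops. Regular contact ends at six months, so some people will have a six-month value and no 12-month value.

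For those people the six-month value is likely to be the best available predictor of the missing one. An ANCOVA on 12-month values alone cannot use it. Adjusting for potential confounders does not help: the six-month value is measured after randomisation, and putting it in the ANCOVA as a covariate would remove part of the treatment effect.

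Two things are at stake: some precision, and protection against bias if attendance at 12 months depends on how people were doing at six.

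**Working it through.** **1. The plan's own figures.** The article gives no figure for the 12-month analysis. Its sample size supplies an effect scale. With "a sample size of 176 participants per group will achieve a statistically and clinically significant 20% difference between the two groups", 80% power and alpha 0.05 (two-sided assumed), the implied standardised difference is

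d = (1.96 + 0.84) × √(2/176) ≈ 0.299 SD.

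A true 12-month effect of 0.30 SD is therefore used below. The total of 460 is reproduced as 352 × 1.30 = 458, whereas 352/0.70 = 503. That is a separate matter from this point.

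**2. Assumptions (not in the article).**
- 230 per arm.
- Correlation between six and 12 months 0.5, 0.7 or 0.85; correlation with baseline 0.4.
- 18% missing by six months, and roughly 15–21% of the remainder lost by 12 months.
- Where loss is selective, the log-odds of loss change by 1.0 per SD of the outcome.
- Later loss is treated as non-attendance by living people.

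**3. People affected.** 460 × 0.82 ≈ 377 are seen at six months and 298–321 at 12 months. The six-month values of 377 − 321 = 56 to 377 − 298 = 79 people go unused. Total loss is then 1 − 321/460 = 30% to 1 − 298/460 = 35%, which is at or above the article's 30% allowance. Any part of the later loss that is death leaves fewer people to whom the point applies, and a smaller gain.

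**4. The two estimators.**
- *ANCOVA:* regress Y12 on arm and baseline among those with Y12; take the arm coefficient.
- *Repeated measures* (likelihood estimate, monotone missingness): b_arm + g × d6. Here b_arm and g are the coefficients of arm and Y6 in the regression of Y12 on arm, baseline and Y6. The term d6 is the arm effect on Y6 among everyone seen at six months.

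**5. Results.** 3,000 simulated trials per scenario. The standard error of either estimate is about 0.10 SD, so simulation error on a bias is about 0.10/√3000 ≈ 0.002. Ranges run over the three correlations.

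| Loss between six and 12 months | ANCOVA bias (SD) | Repeated-measures bias (SD) | Variance ratio (repeated measures / ANCOVA) |
|---|---|---|---|
| Completely at random | about 0 | about 0 | 0.90–0.97 |
| Depends on six-month value, same in both arms | −0.01 to −0.02 | about 0 | 0.93–0.98 |
| Depends on six-month value, controls only | −0.05 to −0.12 | about 0 | 0.92–0.98 |
| Opposite dependence in the two arms (extreme) | −0.13 to −0.26 | about 0 | 0.93–1.02 |
| Depends on unseen 12-month value, controls only | about −0.14 | −0.05 to −0.12 | 0.92–0.98 |

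**6. Cross-check.** A second simulation used correlations 0.75 and 0.45 and about 15% later loss. The ANCOVA estimate was 0.30 under random loss, 0.28 with the same pattern in both arms, and 0.21–0.25 or 0.37 when the pattern differed by arm. The repeated-measures estimate stayed at 0.30, with variance 4–8% lower. The value 0.37 shows that the bias can run in either direction.

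**7. Why the second row is so small.** Losing slower walkers raises the observed mean in both arms by nearly the same amount, and the difference between arms cancels most of it. The residue is 0.01/0.30 to 0.02/0.30, or 3–7% of the effect. In the third row it is 0.05/0.30 to 0.12/0.30, or 17–40%.

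**The case against.** **The article does not say that anyone is dropped.** It names a between-group model and an intention-to-treat principle and gives no missing-data rule. ANCOVA after imputation using six-month values would fit the same text, and such detail is commonly left to a full protocol or analysis plan, neither of which is shown. This stands: exclusion is what the named method does on observed data, not something the article announces. The point survives because the method itself is stated, and a method that uses the six-month data is available.

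**Baseline-adjusted ANCOVA at each visit is a standard method.** True. The plan contains no error or contradiction here; the case is that a better method costs little.

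**A reader might infer that the 12-month estimate is biased whenever slower walkers drop out more.** The results do not support this. With the same pattern in both arms the bias is negligible, and with no treatment effect it vanishes by symmetry.

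**A reader might infer that drop-out will differ by arm.** Participants know their allocation, so it could. But controls receive social visits of equal duration, and the 12-month contact procedure, including the next-of-kin step, is described without distinction by arm. Nothing in the article establishes a difference.

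**A repeated-measures model does not settle deaths.** Also right. Fitted to everyone with a six-month value, it would implicitly project 12-month values for people who had died. A 12-month contrast restricted to survivors cannot come from the same fit as the six-month contrast.

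**Conclusion.** The point holds as a modest improvement to a secondary comparison. As named, and on observed data, the 12-month ANCOVA leaves the six-month values of later non-attenders unused.

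Using them lowers the variance by about 3–10% when loss is random, and by somewhat less in most of the selective scenarios. It also removes a bias of about 0.01–0.02 SD when drop-out depends on six-month status equally in both arms. The larger figure, about 0.05–0.12 SD in either direction, is a sensitivity scenario that needs the dependence to differ by arm. If loss depends on unseen 12-month values, the change reduces the bias without removing it.

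All sizes rest on assumed correlations, loss rates and strength of selection, and shrink to the extent that later loss is death. It would be wrong to read this as a threat to the primary result: someone missing at six months usually has no later value to borrow, so that analysis is little affected.

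**What to change.** For scale outcomes at 12 months, replace the stand-alone ANCOVA with one of the following:

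- a likelihood-based repeated-measures model of the six- and 12-month values, with arm, time, arm × time, baseline value × time and site, and an unstructured covariance; or
- ANCOVA at 12 months after multiple imputation that includes the six-month value.

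Fit the 12-month contrast among people not known to have died by 12 months, as a separate fit from the six-month contrast, and report deaths by arm. Like the planned ANCOVA, this compares survivors, so it should be read beside the death counts.

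Outcomes analysed by logistic regression are not covered by this change; a repeated-measures approach to them would need its own model.

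The cost is a change of wording and a little more programming, with no new data collection. The analysis then assumes that values are missing at random given the observed data, including the six-month value, and the report should say so.

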### Time frame

This study has a 3 year time frame. Recruitment commenced in June of 2007, follow up assessment will continue until September 2009, after which time data analysis will be performed and a final report will be drafted.

## Discussion

The INTERACTIVE trial is among the first to combine nutrition and exercise therapy as an intervention to address the serious consequence of rapid deconditioning and weight loss and subsequent ability to regain pre-morbid function in older patients post PFF. It differs from previous studies in this area in a number of significant ways. Commencement of the intervention will occur sooner than any previous work in an attempt to intercept the rapid deconditioning often observed amongst older adults admitted to hospital. The duration of both components of the study intervention will be longer than any previous work in this area, with weekly follow up over a six month period. This is based on evidence to suggest that weight loss continues for at least 12 weeks following PFF [28] and that training improvements achieved during a 12 week exercise program are lost after the program is completed [21].

The benefits of an exercise program to maintain strength and balance and reduce the risk of falls are well established [13-17], however maintaining patient motivation and adherence to a program is an ongoing challenge faced by therapists. The intensity of the follow up in this trial (fortnightly home visits by the physiotherapist) is greater than the Otago program (consisting of four primarily instructive home visits) due to the need for maintaining sufficient challenge in a clinical group that are likely to increase their ability over time and the complexity of pre-existing medical conditions.

The Otago program is yet to be evaluated amongst patients recovering from PFF and provides a pragmatic alternative to other exercise programs due to its established effectiveness, ease of implementation and affordability.

Through regular supervision attempts will be made to maintain patient motivation, continually set realistic and achievable goals and provide an opportunity to address factors affecting adherence. Another strategy targeted at improving adherence is to involve close relatives or immediate caregivers where appropriate. This comprehensive data collection will provide an opportunity to identify groups most likely to respond to such an intervention, which will then inform future service provision. This trial will also be one of the first to utilise body composition measures obtained through DEXA scans to accurately assess for change in muscle mass following such a comprehensive therapy program administered over six months.

Previous studies have failed to consider the need for provision of an adequate amount of energy and protein to address the deficits associated with pre-existing undernutrition, injury and surgical stress and inadequate dietary intakes during recovery from PFF [26]. A comprehensive approach to nutrition therapy combining education, counselling, dietary modification and supplementation differs from previous work, however was deemed necessary given the lack of evidence that oral supplements alone can improve outcomes in this clinical group [26]. If oral supplements are considered appropriate then they will be prescribed as a medication, an approach that has been observed to improve adherence in older adults [48,49].

This study is also unique in that the impact on caregivers and overall costs and resource use will be carefully measured. Measurement of caregiver strain and burden, quality of life and positive affect over time will provide an opportunity to capture whether the potentially negative impact of frequent visits in the home and possible invasion of privacy are outweighed in the long term by the increased independence and quality of life experienced by the PFF sufferer. The comprehensive analysis relating to both direct and indirect costs of the intervention is also unique and will provide realistic data on the feasibility of the intervention becoming an ongoing service. It is important to provide adequate rehabilitation post PFF to return people as close to premorbid function as possible so that physical decline, hospital re-admission and even residential care admission are avoided. The results of this trial will help to guide the development of more effective rehabilitation programs following PFF, which may ultimately lead to reduced health care costs, and improvements in mobility, independence and quality of life for PFF sufferers.

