The aim of this randomised controlled trial (RCT) is to implement a six month, individualised exercise and nutrition program commencing within 14 days of surgery for PFF, that will result in clinically and statistically significant improvements in terms of physical function, body composition and QOL at an acceptable level of cost and resource use and without increasing the burden of caregivers. Comparisons will be drawn with the attention control group.

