Participants allocated to the attention control group will continue therapy as prescribed during hospital admission (acute and rehabilitation) according to current practice. Social visits of equivalent duration will occur to match the active intervention group. The project physiotherapist and dietitian will provide participants with generic nutrition, exercise and falls information in line with Government recommendations to provide some relevant topics for discussion, this information will also be given to the intervention group.

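### With visit-matched controls, the caregiver comparison cannot show whether frequent home visits are burdensome, although the Discussion says the trial will capture this

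*Protocol article*

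**What the plan says.** The relevant statements in the protocol article are these.

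- **Discussion.** Measuring caregiver strain and burden, quality of life and positive affect over time is presented as a means of finding out "whether the potentially negative impact of frequent visits in the home and possible invasion of privacy are outweighed in the long term". The benefits set against that impact are the patient's greater independence and quality of life.
- **Background, aim.** The programme should succeed "at an acceptable level of cost and resource use and without increasing the burden of caregivers". The next sentence names the comparator: "Comparisons will be drawn with the attention control group".
- **Design overview.** There are two arms, the programme and attention control.
- **Intervention.** For the control arm: "Social visits of equivalent duration will occur to match the active intervention group".
- **Additional Information.** "Monitoring of participants for six months via weekly home visits" is described for participants generally, without restriction to one arm. The Economic evaluation section likewise has a weekly survey of all participants.
- **Baseline, six and 12 month follow-up.** "In addition caregivers will also complete a caregiver burden and strain index".
- **Discussion, on intensity.** The intervention arm has "fortnightly home visits by the physiotherapist". The Intervention section adds fortnightly dietitian review.

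**The concern.** The Discussion names a specific exposure that might harm caregivers: people coming into the home often. A randomised comparison can measure the effect of an exposure only if the arms differ in it. Here the control arm is designed not to differ in contact. That is sound for separating the content of the programme from attention, but it removes the contrast that the Discussion sentence needs.

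What is at stake is the reading of a null caregiver result. If visits are burdensome and the programme content adds little, caregivers in both arms carry the same extra load and the difference is near zero. A reader who takes the Discussion sentence at face value would conclude that the visits do no net harm to caregivers. The same section hopes that the trial's cost data "will provide realistic data on the feasibility of the intervention becoming an ongoing service". A service that replaced ordinary care with the programme would introduce the visits, and the trial would hold no randomised evidence on what they do to caregivers.

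**Working it through.** The plan gives no figure for this point, so there is nothing to reproduce. The question is what the design can identify.

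**1. Between-arm difference.** For mean caregiver burden at six months, let
- b = burden with no visits and no programme,
- V = effect of being visited, common to both kinds of visit,
- C = added effect of the exercise and nutrition programme, including any demand specific to therapy visits.

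Intervention arm: b + V + C. Attention control, if visits are fully matched: b + V.

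Difference = (b + V + C) − (b + V) = C.

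V drops out whatever its size.

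**2. Incomplete matching.** The article matches duration. It does not state the setting or number of control visits. If controls receive a fraction f of the visit exposure, the difference is C + (1 − f)V. For example, with an assumed V of 0.5 SD and f = 0.8, visits contribute (1 − 0.8) × 0.5 = 0.1 SD. Only the unmatched remainder is visible, and it cannot be told apart from C.

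**3. Change over time within an arm.** Let R be the change in burden from baseline to six months due to the patient's recovery.
- Control change: V + R.
- Intervention change: V + C + R.

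That is two equations in three unknowns. Subtracting gives C; V and R appear only as a sum. The change from six to 12 months, after the visits stop, has the same problem: under this model the control change is −V plus further recovery.

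**4. Illustration.** Inputs: 176 per group and alpha 0.05 from Sample Size Considerations; C = 0 and f = 1; V in SD units is assumed. The test is a two-sided normal test with standard error √(2/176) = 0.1066 SD. The probability of a significant result is 1 − Φ(1.96 − d/0.1066) + Φ(−1.96 − d/0.1066), where d is the expected difference.

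| Assumed V (SD) | d against matched controls | P(significant) | d against an unvisited group | P(significant) |
|---|---|---|---|---|
| 0.3 | 0 | 0.05 | 0.3 | 0.80 |
| 0.5 | 0 | 0.05 | 0.5 | 0.997 |
| 0.8 | 0 | 0.05 | 0.8 | about 1.00 |

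The figure of 176 was set for gait speed and is borrowed here; the number of caregivers may be smaller. That would lower the last column but leave the third at 0.05. A larger sample would not help either, because the expected difference against matched controls is zero.

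**The case against.** The best reply is that the sentence is Discussion prose, not a planned test. It speaks of measures over time and of an opportunity to capture something in the long term, which fits a descriptive longitudinal reading. No hypothesis, sample size or primary analysis rests on it. Attention control is also a deliberate and legitimate choice. All of that is fair, and it limits the weight of the point. It does not rescue the sentence: the longitudinal reading confounds visits with recovery (step 3), and the randomised reading loses V (step 1).

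The matching is partly inferred, and that objection also stands. The article does not say that control visits take place at home or equally often, and the intervention arm has a supervised exercise phase of unstated frequency. A reader might infer a visit contrast of exactly zero. The text supports only an intention to match, so the conclusion must be put as holding to the extent that visits are matched.

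Nor is the caregiver comparison empty. Relatives may help with exercise diaries, supplement records and adherence. Those demands differ by arm and are estimated.

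Two stronger readings are tempting and are not supported:
- **That the Background aim is wrong.** It names attention control as its comparator in the very next sentence, and it is correct as written.
- **That the economic result will look falsely cheap because control visits are netted out.** The Economic evaluation section lists the direct costs of the proposed intervention and nowhere says that control visits will be costed. Detailed costing rules belong to the full protocol, which is not shown.

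**Conclusion.** The point holds in a limited form. The Discussion promises an answer on the impact of home visits that a two-arm, visit-matched comparison cannot give. The randomised caregiver difference estimates burden beyond matched visits. Under full matching, visit burden of any size goes undetected, apart from the 5% false-positive rate; under partial matching only the unmatched part enters. A null result cannot support a statement that visits are not burdensome, or that burden is not increased relative to usual care.

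This rests on two assumptions: that the control visits come close to the intervention visits in setting and frequency, as the stated intent to match and the weekly home visits suggest; and that part of the visit burden is the same whether the visit is social or therapeutic. The 0.3 to 0.8 SD range is illustrative and has no source in the article.

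The point concerns the interpretation of a secondary aim. The gait speed outcome, the sample size and the value of the comparison for programme content are untouched.

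**What to change.** 1. In the Discussion, limit the caregiver conclusion to the burden of the exercise and nutrition programme over and above matched attention visits. Withdraw the claim that the comparison captures the impact of the visits. The Background aim needs no change.
2. Add one direct item to the six-month caregiver questionnaire, asking how burdensome and intrusive the home visits were. Report it descriptively by arm, labelled as non-randomised evidence on the visits, so that the stated question has some data behind it.

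The cost is a wording change, one extra item on a questionnaire that caregivers already complete, and a narrower caregiver conclusion. Recruitment began in June 2007 according to the Time frame section, so caregivers already past their six-month assessment would not have the item; the report should state how many were asked. The arms, the sample size and the primary analysis stay as they are.
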